##### Qualitative analyses

Focus group transcriptions will be analysed using a qualitative content analysis, concentrating on the manifest content of exchanges to provide a practical guide for action [32]. Deductive content analysis will be favoured, and barriers and facilitators identified by nurses will be placed into the relevant categories of TICD determinants or other novel, previously unidentified determinants. Fitting with the study’s longitudinal design, these determinants will be tracked over time [33]. Two qualitative data analysts will keep an audit trail of decision-making to allow for verification of the coding process and conclusions, with disagreements resolved by consensus. In addition to focus group data, each event in the facilitator’s logbook will be analysed using a realist analysis approach, assessing the context, mechanism, and outcome (CMO) of each documented change within the context of PEEER cycles. This approach is similar to the theoretical framework developed by Taylor et al. (2014) [34]. All qualitative data will be coded using the qualitative data management software, Atlas.ti version 8. The trustworthiness of the results will be verified by examining the analysts’ audit trails, presenting the results to nurses, and checking for consistency with the implementation outcomes.

##### Mixed-methods analyses

To guide the mixed-methods analyses, we will create a mixed-methods matrix whereby identified TICD determinants are mapped onto implementation outcomes. This was based on a causal chain developed to understand interrelationships between overall effectiveness and selected provider-related implementation outcomes (Additional file 3) [23]. This causal chain will also guide interpretation of our implementation outcomes.

After study completion, qualitative data and quantitative data will be presented together for each time point. Guided by the mixed-methods matrix, qualitative data will be used to provide nuance and context for the interpretation of quantitative data. Further context for nursing-related qualitative and quantitative results will be obtained from the qualitative analysis of changes documented in the internal facilitator’s logbook.

One of two results would suggest the viability of Lost & Found for trialing, ideally as a multisite stepped-wedge randomised study: (1) high and relatively stable overall scores for implementation outcomes throughout the study or (2) an overall increasing trend culminating in high end-of-study implementation outcome scores. Each of these would also be supported by qualitative data from focus groups with nurses.

### AIM 2: To evaluate cumulative effectiveness and sustainability

#### Overview

Three analyses will be undertaken:
i)A descriptive analysis of cumulative effectiveness during the implementation and sustainability phases;ii)A pre-post evaluation of the proportion of OOC patients who are re-engaged during the implementation phase compared to the proportion of OOC patients in the year (2017–2018) prior to the implementation phase (2018–2019); andiii)A pre-post evaluation of the proportion of OOC patients who are re-engaged during the sustainability phase compared to the last 3 months of the implementation phase.

#### Participants

All MUHC patients in the RISQ database during the 12-month implementation phase and the first three months of the sustainability phase will be included in analysis i). For analysis ii), we will retrospectively apply the OOC-RPT, excluding the nurse validation step, to patients in the year prior to implementation in order to create a pre-implementation comparison group. Thus, we will include all patients categorised as OOC by the OOC-RPT from one year prior (2017-2018) and to the end of the implementation phase (late 2019) in this analysis. Patients labelled as OOC before or after this time frame will receive the Lost & Found intervention, but will be excluded from the analysis because they did not become OOC within the time frame of the analysis. Based on the number of patients who were identified as not having had care appointments in 2016, we estimate approximately 25–30 patients will be identified as potentially OOC each month during the implementation of Lost & Found. In analysis iii), MUHC patients categorised as OOC from three months before the end of the implementation phase to the end of the sustainability phase (three months) will be included.

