### Core element II: Contacting OOC patients

Clinic nurses will telephone patients using available contact information (RISQ, other hospital databases). They will receive a half-day of training from an expert in motivational communication, an essential skill for motivational interviewing. This training will help nurses encourage re-engagement through effective questioning, empathy, non-judgemental curiosity, guiding language, and adapted messaging [18]. This training is intended to provide nurses with additional skills or to strengthen existing skills for phone calls. It will be used at their discretion.

Patients who are reached by telephone will be scheduled for an appointment within timeframes dependent on their OOC-RPT risk category. However, earlier follow-up may be necessary as determined by clinical judgement. Patients in the high-risk category will be scheduled to be seen by a clinic nurse within 24-48 hours for basic primary care and phlebotomy (laboratory testing), and with their regular physician provider within one week of the nursing visit, for a full clinical assessment. Should the clinical situation suggest a need for more urgent care, the patient will be assessed by the walk-in physician on the same day as the nursing visit. Patients in the intermediate-risk category will be scheduled for an appointment within approximately two to four weeks of the telephone call, while patients in the low-risk category will be seen within four to six weeks. Patients who miss a scheduled appointment will be contacted the same day and provided another appointment, within timeframes depending on their risk category.

Attempts to contact patients will be made every 1, 2, and 4 weeks, for the high-, intermediate-, and low-risk categories, respectively. This pattern will be repeated until patients are contacted. Attempts to re-engage unreachable OOC patients will continue for up to 6 months (based on the maximum time a person can be outside of Quebec and still retain health care coverage), after which no further contact attempts will be made [19]. Nonetheless, these patients will remain on the OOC list until they return to care or until there is sufficient information to determine their care status. In all cases, nurses can modify the contact frequency and/or period based on individual patient factors.

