#### Outcomes and related measures

##### Effectiveness

Information to evaluate changes in interim effectiveness outcomes over time will be collected automatically using RISQ and will be extracted for analysis at specific time points during the study (see Table 2). Interim effectiveness refers to effectiveness between the time points in Table 2, as opposed to cumulative effectiveness, which refers to overall effectiveness for the implementation or sustainability phases. These interim effectiveness outcomes include the number of patients identified and confirmed as OOC by nurses. Among OOC patients, we will report the number of patients contacted, successfully re-engaged, and not re-engaged, as well as reasons for lack of care re-engagement. For each OOC-RPT risk category, and overall, we will also provide the number of contact attempts needed to re-engage patients, time to re-engagement, and other clinical and sociodemographic information routinely collected in RISQ.

**Table 2 Tab2:** Data collection schedule

	Pre-implementation	Week 1	Week 2	Week 3	Week 4	Month 2	Month 3	Month 6	Month 12	Month 15
Effectiveness					d	d	d	d	d	d
Feasibility	a, c				a, c	a, c	a, c	a, c	a, c	c
Acceptability	a, c				a, c	a, c	a, c	a, c	a, c	c
Adoption	a, c				a, c	a, c	a, c	a, c	a, c	c
Fidelity	b, c	b	b	b	b, c	b, c	b, c	b, c	b, c	c

a) 36-item questionnaire; b) fidelity checklist; c) focus group; and d) RISQ

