### Outcomes and related measures

#### Effectiveness

For i), the same effectiveness outcome measures detailed in Aim 1 will be used to report on cumulative effectiveness during the implementation phase (months 1 to 12) and for the sustainability phase (months 12 to 15) (Table 2). Re-engagement into care among OOC patients is the primary outcome of interest for ii) and iii).

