This analysis is similar to the one detailed in ii) but compares effectiveness during the three-month sustainability phase to the last three months of the implementation phase. The analysis also differs in that the nurse validation step of the OOC-RPT will be included in each arm since manual changes to follow-up status is possible in both arms. We hypothesise that few changes will be made to peripheral components of Lost & Found in the last three months of the implementation phase, suggesting the intervention will be comparable to that which is delivered in the sustainability phase.

The same model (Equation 1) will be used to assess short-term sustainability of Lost & Found, where *Imp* = 1 indicates that the patient was OOC during the sustainability phase and 0 for the last three months of the implementation phase. A finding of no statistically significant difference in the probability of re-engagement for OOC patients in the implementation or sustainability phases will suggest short-term sustainability of Lost & Found.

All analyses will be conducted using R statistical software.

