## Abbreviations

CVIS: Combination antiretroviral therapy
DSQ: Dossier santé Québec
EMR: Electronic medical record
HCV: Hepatitis C virus
HIV: Human immunodeficiency virus
MUHC: McGill University Health Centre
MSM: Men who have sex with men
OOC: Out of care, representing absenteeism from HIV care beyond what is expected for clinical status
PLHIV: People living with HIV
PWID: People who inject drugs
Re-engagement: Patients will be considered “re-engaged” in care if they re-present to the MUHC following a period of absenteeism
Retention: Patients will be considered “retained” in care if they remain in care one year following re-engagement
RISQ: Réseau d’informations scientifiques du Québec
VL: Viral load

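### Analysis iii sets no outcome window from the OOC flag and keeps entry open to Month 15, the last listed RISQ extraction, so late entrants are barely observed and follow-up may differ between arms

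*Protocol article*

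**What the plan says.** - Entry (Aim 2, Participants): analysis iii takes those flagged in the following span: "from three months before the end of the implementation phase to the end of the sustainability phase (three months) will be included". The Aim 2 Effectiveness section dates the later phase: "for the sustainability phase (months 12 to 15) (Table 2".
- Outcome: "Re-engagement into care among OOC patients is the primary outcome of interest for ii) and iii". The Abbreviations count patients as re-engaged "if they re-present to the MUHC following a period of absenteeism". No time limit from the OOC date is attached.
- Data (Aim 1, Effectiveness): RISQ data "will be extracted for analysis at specific time points during the study (see Table 2". The last column of that table is Month 15.
- Arms (Aim 2, Data analysis iii): *Imp* = 1 "indicates that the patient was OOC during the sustainability phase and 0 for the last three months of the implementation phase". Arms are set by when the patient was OOC. The model offset is the number of OOC patients, so there is no person-time term.
- Comparison (Aim 2, Overview): the "proportion of OOC patients who are re-engaged during the sustainability phase compared to the last 3 months of the implementation phase".
- Timing of visits (Core element II): once reached, high-risk patients see a nurse in 24–48 hours. Intermediate-risk patients are booked "within approximately two to four weeks of the telephone call, while patients in the low-risk category will be seen within four to six weeks". Calls are repeated every 1, 2 or 4 weeks by risk category, for up to 6 months.
- Decision (Data analysis iii): absence of a significant difference is taken to suggest short-term sustainability.

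**The concern.** Entry closes on the day of the last listed data cut, but the outcome is a visit that the programme itself places weeks after a successful call. Patients flagged late in the sustainability phase therefore have little time to be observed returning. Those flagged in the last implementation quarter could have 13 weeks more, if their outcomes are also counted to Month 15. Nothing in the model corrects unequal follow-up, and the text does not say when counting stops for the comparison arm.

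Analysis iii is the only pre-post test of sustainability. On one permitted reading the calendar alone pulls the risk ratio below 1. On another the arms are balanced but both proportions are too low. The same data could then support opposite conclusions.

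**Working it through.** The protocol gives no sample size, power or expected re-engagement rate for analysis iii, so there is no stated figure to reproduce.

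**Step 1: follow-up at Month 15, from the protocol's intervals.** Take each three-month phase as 13 weeks, with even entry. The share of sustainability entrants with less than L weeks of follow-up is L/13:
- L = 2: 2/13 = 15%
- L = 4: 4/13 = 31%
- L = 6: 6/13 = 46%

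The 2–4 week figures are the call-to-visit interval for intermediate risk, and the 4–6 week figures that for low risk. They assume the first call succeeds on the day of the flag. Mean follow-up is 13/2 = 6.5 weeks in the sustainability arm. In the comparison arm counted to Month 15 it is 6.5 + 13 = 19.5 weeks.

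**Step 2: an unchanged programme, both arms counted to Month 15.** Simulation with 400,000 patients per category, flags uniform over 13 weeks, and the protocol's call spacing and booking intervals. Assumed, not in the protocol: first call on the day of the flag, 40% reached per call, 80% attendance, no spontaneous returns.

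| Risk category | Sustainability | Last implementation quarter |
|---|---|---|
| High | 69.6% | 80.0% |
| Intermediate | 44.6% | 78.6% |
| Low | 25.8% | 69.1% |

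The risk mix (high/intermediate/low) is not given, so three are tried:
- 20/30/50: (0.2×69.6 + 0.3×44.6 + 0.5×25.8) = 40.2% v (0.2×80.0 + 0.3×78.6 + 0.5×69.1) = 74.1%; RR = 0.54
- 60/30/10: 57.7% v 78.5%; RR = 0.73
- all high risk: 69.6% v 80.0%; RR = 0.87

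Varying reach as well, the lowest RR is 0.45 (20% reached, 20/30/50) and the highest 0.93 (60% reached, all high risk). It stays below 1 throughout.

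**Step 3: chance of a falsely significant fall.** Two-sided 0.05 is assumed, since no level is stated. Unadjusted Wald test of log RR:

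SE = √[(1−p₁)/(n·p₁) + (1−p₀)/(n·p₀)]; chance = Φ(|ln RR|/SE − 1.96)

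The protocol expects 25–30 potentially OOC patients a month, or 75–90 a quarter, before nurse validation. Analysis iii applies validation, and the Limitations cite other studies in which most flagged patients were not truly OOC. If more than half drop out, fewer than about 38–45 remain per arm. The calculation uses 30 and 45.

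For 20/30/50 at n = 30: SE = √(0.598/12.06 + 0.259/22.23) = 0.247; |ln 0.5425| = 0.612; Φ(0.612/0.247 − 1.96) = Φ(0.51) = about 70%. The same formula gives:

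| Mix (40% reached) | n = 30 per arm | n = 45 per arm |
|---|---|---|
| 20/30/50 | 70% | 86% |
| 60/30/10 | 39% | 54% |
| All high risk | 15% | 20% |

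**Step 4: each arm counted only within its own quarter.** Both arms then have 0–13 weeks of follow-up and the expected RR is 1.00. With the 20/30/50 mix, however, only 38–61% of eventual programme returns are seen as reach goes from 20% to 60%.

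**Step 5: equal window from the flag.** The expected RR is 1.00. In a separate simulation with equal true proportions (75–90 per arm), about 2% of trials showed a significant fall, as a two-sided 0.05 test should.

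**The case against.** The strongest reply is that the Aim 2 Overview can be read as counting re-engagement inside each quarter. The Effectiveness section separates months 1–12 from 12–15, and Table 2 has a Month 12 extraction. On that reading the arms are truncated alike and there is no differential bias. This stands. A reader might infer that the sustainability test is bound to set a mature arm against an immature one, but the documents do not fix that. They also do not exclude it, because arms are assigned by OOC date and no cut-off is stated for the comparison arm.

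Other points stand in part:
- Table 2's schedule is described under Aim 1 and cited in Aim 2 for analysis i. Nothing forbids a later extraction for analysis iii, but none is listed.
- A reader might take 75–90 per arm and conclude that a false fall is almost certain: 97–99% with 40% reached and the 20/30/50 mix. Those counts precede nurse validation, so the documents do not support that figure.
- Reach, attendance and risk mix are assumptions, and the mix matters greatly. High-risk patients are affected least.
- It is too strong to say that late low-risk entrants cannot be counted. Earlier follow-up is allowed on clinical judgement, and any re-presentation to the MUHC counts.
- This is a pilot without a power calculation, and its stated viability criteria for implementation rest on implementation scores. That lowers the severity.

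It could also be said that an article leaves outcome windows to a fuller document. But the entry dates, the last listed extraction, the arm rule and the offset are all stated here, and together they create the problem.

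**Conclusion.** The point holds as a should-fix. What follows from the text, given even entry, is that 31% of sustainability entrants have under 4 weeks and 46% under 6 weeks before the last listed extraction, with no common outcome window.

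The bias between arms is conditional. It arises if both arms are counted to Month 15, and then acts against the sustainability arm, with RR about 0.45–0.93 for an unchanged programme. The chance that this reaches significance runs from about 15% to 86% over the mixes shown at 40% reached and 30–45 confirmed patients per arm. Where it does not reach significance, the rule would still read as sustained, but from a risk ratio that is too low. If each arm is closed at the end of its own quarter, the comparison is fair and the loss is in the returns never seen.

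**What to change.** In analysis iii, define re-engagement within one prespecified window from the OOC flag, of the same length for every patient in both arms. State the length, and make it long enough to cover the longest call-to-appointment interval in Core element II. Keep entry closing at Month 15 and add one RISQ extraction, for outcomes only, one window-length later.

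If a later extraction is not possible, close entry the same number of weeks before the end of each quarter, so that every included patient has the full window.

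Cost: results come later by the length of the window. With the fallback the sample shrinks instead; a 6-week window, for example, would keep (13 − 6)/13 = 54% of entrants. Returns after the window are not counted, which matters because contact attempts may run to 6 months. With the later extraction, the window of patients flagged late in month 12 runs into the sustainability phase, and the plan should say so. No clinical procedure changes.

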### Outcomes and related measures

#### Effectiveness

For i), the same effectiveness outcome measures detailed in Aim 1 will be used to report on cumulative effectiveness during the implementation phase (months 1 to 12) and for the sustainability phase (months 12 to 15) (Table 2). Re-engagement into care among OOC patients is the primary outcome of interest for ii) and iii).

#### Data analysis

i)Descriptive analysis

To assess cumulative effectiveness during implementation and sustainability, descriptive statistics (e.g. counts, proportions, medians, and inter-quartile ranges) will be reported.
ii)Pre-post analysis: Implementation phase

For this analysis, the second step of the OOC-RPT – nurse validation - will be ignored to ensure comparability between the two groups. This is done because nurse validation was not possible prior to the implementation of changes to the RISQ software. While this will result in a non-differential bias (to the null), it will simultaneously prevent a possible differential bias introduced from the nurse validation step of the OOC-RPT. To account for the impact that contact attempts could have on future follow-up behaviours, we will consider only the first OOC event for each patient. We will compare the re-engagement rates of OOC patients identified from our retrospective application of the OOC-RPT in the pre-implementation phase to re-engagement rates of OOC patients identified by step 1 of the OOC-RPT in the implementation phase. If the intervention is effective, we will find a statistically significant difference in the probability of re-engagement for OOC patients during the 12-month implementation phase compared to the year prior.

The impact of the complete Lost & Found intervention (i.e. both core elements) and implementation strategy on the proportion of OOC patients re-engaged will be examined in a Poisson model with robust variance estimation, using the year prior to implementation for comparison (see Eq. 1):
1$$ \log \left(\mathrm{R}\right)={\upbeta}_1\ast \mathrm{Imp}+{\upbeta}_2\ast \mathrm{Sex}+{\upbeta}_3\ast \mathrm{Age}+{\upbeta}_4\ast \mathrm{Canada}+\upmu +\log \left(\mathrm{C}\right) $$

where *R* is a count of number of patients re-engaged into care, *Imp* is a dummy variable, where *Imp* = 1 indicates that the patient was OOC during the implementation phase and 0 for the pre-implementation phase, *Sex* accounts for the possible differences in the proportion of men and women in the pre-implementation or implementation phases, *Age* accounts for differences in the ages of patients between the two periods, and *Canada* accounts for differences between the two periods for the proportion of patients born outside of Canada, which may be of concern given a recent influx of refugees into our clinic. *log(C)* is considered the “offset” in the Poisson regression model, where *C* is the number of patients OOC over the two periods. We assume that Lost & Found will not impact the rate at which patients are categorised as OOC in the implementation phase and will verify this assumption prior to conducting the analysis. Potential other variables for inclusion in the model will be selected to adjust for possible temporal shifts in the patient population (i.e. factors that could affect engagement in care.) Due to lacking information in the pre-implementation period (e.g. number of patients confirmed as OOC by nurses, information about re-engagement efforts) it is not possible to consider the relative overall effectiveness of each core element.

The overall effect of the intervention and implementation strategy on the proportion of re-engaged OOC patients will be determined from the log of the *β*_*1*_ coefficient, providing a risk ratio for the probability of re-engaging OOC patients through the use of Lost & Found.

We did not conduct a sample size calculation due to uncertainty for several study parameters, including effect and sample sizes. The results of this analysis will inform power calculations for a larger study. Thus, while a statistically significant result would suggest that Lost & Found is viable for further evaluation, a statistically non-significant result would not necessarily rule it out since such a result may only be due to insufficient power.
iii)Pre-post analysis: Sustainability phase

This analysis is similar to the one detailed in ii) but compares effectiveness during the three-month sustainability phase to the last three months of the implementation phase. The analysis also differs in that the nurse validation step of the OOC-RPT will be included in each arm since manual changes to follow-up status is possible in both arms. We hypothesise that few changes will be made to peripheral components of Lost & Found in the last three months of the implementation phase, suggesting the intervention will be comparable to that which is delivered in the sustainability phase.

The same model (Equation 1) will be used to assess short-term sustainability of Lost & Found, where *Imp* = 1 indicates that the patient was OOC during the sustainability phase and 0 for the last three months of the implementation phase. A finding of no statistically significant difference in the probability of re-engagement for OOC patients in the implementation or sustainability phases will suggest short-term sustainability of Lost & Found.

All analyses will be conducted using R statistical software.

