## Abstract

**Background:**

At the McGill University Health Centre (MUHC), 10% of patients living with HIV do not return for care annually. Currently, no formal system exists to re-engage out-of-care (OOC) patients. Lost & Found, developed using an implementation science approach, is an intervention to re-engage OOC patients. It is based on existing evidence-based interventions and will be adapted for use by nurses at the MUHC. The aims of this study are to simultaneously assess both implementation and effectiveness of Lost & Found in order to determine the viability of a future multisite stepped-wedge cluster randomised trial.

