## Background

The UNAIDS 90-90-90 targets have set ambitious and necessary global goals for improving the HIV care cascade and tackling the HIV epidemic by 2030 [1]. The latter two targets seek to ensure that 90% of people diagnosed with HIV are prescribed combination antiretroviral therapy (cART) and that 90% of these people have suppressed HIV viral loads (VL). To accomplish these objectives, people living with HIV (PLHIV) must be engaged in care.

The cascade of HIV care has been assessed at the McGill University Health Centre (MUHC) in Montreal, Quebec. Since 2015, 10% of registered patients have not returned for care annually [2]. Furthermore, a formal system to re-engage these patients does not exist. Given the individual- and population-level health impacts associated with suboptimal HIV treatment adherence, as well as the socioeconomic repercussions, attrition from the HIV care continuum must be minimised [3–5]. Therefore, developing and testing interventions to re-engage PLHIV into care should be prioritised.

Criteria used for defining and identifying patients as out-of-care (OOC) vary greatly. For example, definitions based on absenteeism differ on the time period selected, from a few months to greater than a year [3, 6–9]. Also, these definitions do not account for relevant clinical factors such as CD4 cell counts, viral load test results, and comorbidities, all of which may influence risks for negative HIV-related outcomes.

A definition for OOC that combines time- and patient-related characteristics could better inform patient-level HIV care trajectories. Using electronic medical record data on medication adherence, last care appointment, substance use, recent CD4 count, prior cART exposure, and treatment failure, Robbins et al*.* created a Risk Prediction Tool (RPT) to predict and stratify patients by risk of HIV viremia [10]. This RPT was later used to effectively predict patients’ risk of missing HIV care appointments [11].

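### As written, keeping one first OOC event per patient over a pooled two-year set drops repeat-OOC patients from the implementation arm only, so the arms differ in prior OOC history

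*Protocol article*

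**What the plan says.** Aim 2, Participants, sets one analysis population for analysis ii): "we will include all patients categorised as OOC by the OOC-RPT from one year prior (2017-2018) and to the end of the implementation phase". Patients labelled OOC outside that span still receive the intervention but "will be excluded from the analysis because they did not become OOC within the time frame of the analysis".

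Aim 2, Data analysis, ii) Pre-post analysis: Implementation phase, then restricts the events: "we will consider only the first OOC event for each patient". The reason given is "To account for the impact that contact attempts could have on future follow-up behaviours". The same paragraph sets aside nurse validation so that the two groups can be compared on the same footing.

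In Equation 1 the arm indicator is Imp, where 1 "indicates that the patient was OOC during the implementation phase and 0 for the pre-implementation phase". The named covariates are sex, age and birth in Canada. Further variables are left open, to adjust for shifts over time in the patient population. The article also says it will verify, before the analysis, that Lost & Found does not change the rate at which patients are categorised as OOC.

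**The concern.** The restriction is not said to apply within each period. Applied to the pooled set, it uses the pre-implementation year as a look-back for the implementation arm, and the pre-implementation arm gets no matching look-back. Prior OOC history is then present in one arm and removed from the other by the analysis rule itself.

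Prior history is plausibly related to the outcome. A second OOC event requires a return after the first, and the Abbreviations section defines re-engagement as coming back to the centre after an absence. Everyone removed has therefore re-engaged once and lapsed again. Re-engagement is the primary outcome of this analysis, and its result is meant to inform both the viability of a larger trial and that trial's power calculation, so an artefact here would carry forward.

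**Working it through.** The article gives no sample size, power or overlap figure for this analysis, so there is no stated figure to reproduce.

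**1. Trace the rule through the event patterns (pooled reading).**
- Two events in the pre-implementation year: patient kept in the pre-implementation arm.
- Two events in the implementation year: patient kept in the implementation arm.
- One event in each year: patient kept in the pre-implementation arm, dropped from the implementation arm.
- One event before the window, resolved, then one in the pre-implementation year: patient kept in the pre-implementation arm.

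At patient level, removal is one-sided.

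**2. Arm size.** From Aim 2, Participants: 25 to 30 potentially OOC patients per month, so N = 12 × 25 = 300 to 12 × 30 = 360, taken as distinct patients. Let r be the share of implementation-year OOC patients who were also OOC in the prior year (assumed). Arm size = N(1 − r).
- r = 10%: 300 × 0.9 = 270 to 360 × 0.9 = 324.
- r = 20%: 300 × 0.8 = 240 to 360 × 0.8 = 288.

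**3. Risk ratio with no intervention effect.** Assume a steady state, so that a share r of the pre-implementation arm also had a prior-year episode. Let pN and pR be the re-engagement probabilities without and with such an episode. Then RR = pN / [(1 − r)pN + r·pR]. With pN = 0.40 (assumed):

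| r | pR = 0.20 | pR = 0.40 | pR = 0.60 |
|---|---|---|---|
| 10% | 0.40/0.38 = 1.05 | 1.00 | 0.40/0.42 = 0.95 |
| 20% | 0.40/0.36 = 1.11 | 1.00 | 0.40/0.44 = 0.91 |

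**4. Power, for illustration only (40% against 50%, assumed).** With 300 per year, power falls from 0.69 to 0.67 (r = 10%) or 0.64 (r = 20%). With 360 per year, it falls from 0.77 to 0.75 or 0.72. The loss is modest; the asymmetry matters more.

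**5. Simulations with no intervention effect (assumed patient mixes, clinic of 1777).**
- If 20% of patients leave at 50% a year and return at 80%, and the rest leave at 10% and return at 40%, the pooled rule gives RR 0.93 and an implementation arm of 225. First event per period gives 1.00 and 287.
- Three other mixes moved the RR from 1.012 to 1.020, from 1.010 to 1.013, and from 1.013 to 0.988, so by no more than about 2.5%.
- If OOC-prone patients re-engage less often (about 330 OOC a year, coefficient of variation of OOC risk 1), RR is 1.06 and 31% of the arm is removed. That overlap is probably at the upper end, because a repeat needs a lapse, a return and a further lapse inside about 24 months.

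The sign changes with the mix.

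**6. The OOC-rate check.** If it is run on the first-event data, 300 in one year is compared with 270 in the next at r = 10%, a ratio of 0.90 although the true rate is unchanged.

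**The case against.** **The pooled reading is an inference.** The sentence does not say that first means first across both years, and the text goes on to describe two groups identified separately. If first means first within each period, the problem disappears. That stands as an ambiguity. But the population is defined as one span and the rule is one event per patient, so an analyst following the text would build the asymmetric dataset.

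**The rationale has some force.** A reader might infer that it cannot apply to pre-implementation events, since "a formal system to re-engage these patients does not exist". The documents do not support that. Core element II keeps unreached patients on the OOC list, and Aim 2, Participants, offers the intervention even to those labelled OOC before the window. It follows that patients from the pre-implementation year who are still absent at launch can be called. The Background also describes earlier informal attempts by nurses. Some second events in the implementation year may therefore follow a contact, and clustering the variance would not remove that carry-over. What does not stand is using this reason to remove every patient with a pre-implementation event, including those who returned unaided before launch.

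**The exclusion of patients labelled OOC before the window might purge the pre-implementation arm too.** The reason stated for it concerns onset outside the window. It does not reach a patient whose earlier episode resolved and who became OOC again inside the window.

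**This is a pilot, and its limitations section concedes uncontrolled confounding.** That is fair, and further covariates are allowed. But this imbalance comes from the analysis rule, and no covariate can restore a stratum that is absent from one arm.

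**Conclusion.** The point holds for the plain reading of the two Aim 2 passages together. The rule leaves the arms unlike in prior OOC history, works against the comparability that the same paragraph seeks, and reduces the implementation arm.

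The size is conditional. With 10% to 20% overlap and a 20-point difference in re-engagement either way from 40%, the no-effect risk ratio lies between 0.91 and 1.11. It is 1.00 if repeaters re-engage at the same rate, and several simulated mixes shift it by 3% or less. Overlap and re-engagement among repeaters are assumptions, because the article gives neither.

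A reader might infer that, because the removed patients have already returned once, the rule must understate the intervention's effect, or that it invalidates the comparison. The documents support neither: the sign depends on who repeats, and the amount may be small.

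**What to change.** State whether the first event is counted per period or across both, and treat the periods alike. There are two workable options.

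- **First OOC event within each period.** A patient may contribute once to each arm, with the robust variance clustered on patient. Add a sensitivity analysis that leaves out implementation-year events following a Lost & Found contact for an earlier OOC episode. Cost: mild within-patient correlation, which the clustering handles, and possible carry-over from contact, which only the sensitivity analysis addresses.
- **The same 12-month look-back for both arms.** Run step 1 of the OOC-RPT on the year before the pre-implementation year and exclude prior-year OOC patients from both arms. Cost: a smaller pre-implementation arm and one more year of retrospective data.

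Under either option, report the number of patients removed per arm, and run the planned check on the OOC rate before any first-event restriction. The text change is a few sentences.
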